#### **9.1.2.3 Sample Size Calculation**

Sample size was calculated using G\*Power 3.1. Assuming that the data is normally distributed, this study will use mixed model ANOVA to compare differences between

the effects of DD-10, S-10, and S-0 pressure garment on sensorimotor functions and quality of life among stroke patients at three different time points during the 8 weeks of application. With small to medium effect size,  $f$  of 0.125, power of 0.8,  $\alpha$  error of 0.05, three groups, and three measurements, the total sample size needed will be 132, as shown in Figure 4. With 44 people in each group and taking into account the 20 % dropout rate, by using the formula:  $N = n/(1-d)$ , i.e.,  $44/(1-0.2) = 55$ , there will be a total of 55 people in each group. Thus, the final sample size will be 165 patients ( $n$ : DD-10 Group = 55; S-10 Group = 55; S-0 Group = 55).

[figure not shown]

Figure 4. Sample Size Calculation

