| 17:00 – 17:30 | Q&A                                                                                 |

For randomization purposes, the researcher will generate 165 sequences that contains equal numbers of 1 (S-10), 2 (DD-10), and 3 (S-0) using a computerized software SPSS 26.0. The sequence will be store electronically. The process of data

collection will then proceed with participant recruitment. This recruitment will be done by placing posters that contain the relevant information of this study, including the study objectives, procedures, and duration alongside contact information, etc. in the three hospitals as permitted. Interested patients can contact the researcher of this study. Recruitment will also be done through recommendation made by therapists who are involved in treating stroke patients. Before enrolling into the study, potential participants will be screened using MAS, SLUMS, and BRS by Therapist A. Only those who meet the inclusion will be enrolled. Prior to the enrolment, the potential participants will need to read the information sheet (Appendix L) and sign the written informed consent form (Appendix M). Participants will be asked to complete the Demographic Form (Participant) (Appendix A).

After participant enrolment, Therapist A will report to the researcher to obtain the randomization sequence number generated using SPSS 26.0. The researcher will assign the participant into either S-10 (intervention group), DD-10 (intervention group), or S-0 (placebo group) according to the sequence list. Therapist A, a blinded therapist will then proceed with taking the baseline data or Time 1 (start of trial), including FMA, BBT, MAS, VAS, DASH, and SF-36. After that, Therapist A will take the pressure garment measurement and then, give the pressure garment measurement to the pressure garment fabricator for pressure garment custom fabrication. Upon receiving the two pairs of pressure garment (within 7 days after pressure garment measurement), the participant will try it on for 30 minutes, under the supervision of Therapist B, a blinded therapist. The participant will formally be enrolled in the study if he/she does not experience allergy, oedema, pain or any other discomfort. All participants will be asked to wear the provided pressure garment for 3 hours in the morning, 3 hours in the afternoon, and 8 hours at night each day for 8 weeks.

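### The arm is assigned before the assessor records the Time 1 outcome scores, including the primary FMA-UE, and the same assessor obtains the sequence number

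*Protocol*

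**What the plan says.** Section 9.1.5 (Data Collection) sets out these steps:

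1. Therapist A screens with MAS, SLUMS and BRS. Consent is obtained, and the Demographic Form is described at this stage.
2. "After participant enrolment, Therapist A will report to the researcher to obtain the randomization sequence number generated using SPSS 26.0".
3. The researcher assigns S-10, DD-10 or S-0 from the list.
4. "Therapist A, a blinded therapist will then proceed with taking the baseline data or Time 1 (start of trial"). This covers FMA, BBT, MAS, VAS, DASH and SF-36.
5. "After that, Therapist A will take the pressure garment measurement", which goes to the fabricator. The garments arrive within 7 days and are tried on for 30 minutes under Therapist B.

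The same section defines the list entries as 1 (S-10), 2 (DD-10) and 3 (S-0). It describes Therapist A as a blinded assessor. Section 9.1.4.3 names the FMA of the upper extremity as the primary outcome. Sections 5.0, 9.1.2.3 and 9.1.6 together place Baseline, Week 4 and Week 8 in a mixed model ANOVA. On size, section 9.1.2.3 states: "three groups, and three measurements, the total sample size needed will be 132".

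**The concern.** A baseline score is fully protected from allocation only if it is recorded before allocation exists. Here the protection rests on masking alone, and the procedure puts strain on that masking. The person who asks for the sequence number is the person who goes on to score the examiner-rated primary outcome and measure the limb. The list entries are arm codes, and nothing says that Therapist A receives only a list position.

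If the arm leaked at this point, Time 1 scores could shift in one arm. Because Time 1 is one of the analysed measurements, a shift at that visit alone would look like a different course over time between arms. It could create an apparent garment effect or hide a real one. The protocol does plan to check Therapist A's masking, but only at Week 8, after the Time 1 values are fixed.

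**Working it through.** **Step 1: which test is the trial sized for?** Inputs from section 9.1.2.3 are effect size f "of 0.125, power of 0.8", then "error of 0.05, three groups, and three measurements, the total sample size needed will be 132". The text gives neither the between-visit correlation nor the sphericity correction (Figure 4 is not shown), so I assume correlation ρ = 0.5 and ε = 1.

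For the group-by-time interaction with k = 3 groups and m = 3 visits:

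- λ = f²·N·m/(1−ρ) = 0.015625 × 132 × 3 / 0.5 = 12.375
- df1 = (k−1)(m−1) = 4 and df2 = (N−k)(m−1) = 258
- power = 0.808 at N = 132, and 0.7975 at N = 129

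So 132 is the smallest multiple of three that reaches 0.80. Under the same assumptions, a within-factor main effect needs 105 and a between-group main effect needs 417. Neither matches. Dropout inflation is 44/(1−0.2) = 55 per arm, or 165, as stated. The protocol does not use the phrase group-by-time. It is inferred from the three-visit mixed ANOVA and from this match.

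**Step 2: what would a shift confined to Time 1 do?** Assume no true effect, SD 1, equal correlation ρ between visits, n = 44 per arm, and one arm's Time 1 mean moved by b SD with Weeks 4 and 8 untouched. In a 3×3 table with one shifted cell, the interaction sum of squares is b²(1−1/3)(1−1/3) = (4/9)b². Hence

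λ = n·(4/9)·b²/(1−ρ), referred to F with 4 and 258 df.

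For b = 0.2 and ρ = 0.5: λ = 44 × 0.4444 × 0.04 / 0.5 = 1.56, giving a rejection rate of 14.0% for the nominal 5% test. Neither b nor ρ is in the protocol, so the range is:

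| ρ (assumed) | b = 0 | b = 0.1 | b = 0.2 | b = 0.3 |
|---|---|---|---|---|
| 0.5 | 5% | 7.0% | 14.0% | 27.9% |
| 0.7 | 5% | 8.4% | 21.2% | 45.3% |
| 0.8 | 5% | 10.3% | 30.8% | 64.3% |
| 0.9 | 5% | 16.6% | 58.5% | 93.3% |

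**Step 3: when is there no effect?** With b = 0 the rate is 5% in every row. If one arm is shifted by the same amount at all three visits, the shift is a pure group effect, the interaction residuals are zero, and this test again stays at 5%. The inflation therefore needs both disclosure of the arm and a scoring shift that differs between Time 1 and the later visits.

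**The case against.** The strongest objection is that Therapist A is stated to be blinded and that no garment has been made or worn at Time 1. The garment cannot have changed the scores. Only knowledge of the arm can, and the protocol does not say that Therapist A learns it. This stands: the order of steps alone biases nothing, and the error rates in the table are conditional. If the number obtained is in fact the arm code, the larger defect is disclosure to the assessor, which reaches Weeks 4 and 8 too.

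Four stronger readings are tempting and are not supported:

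- **That every baseline value is taken after assignment.** The screening MAS, SLUMS and BRS come before it, and the Demographic Form is described before it. The point covers the Time 1 outcome scores and the garment measurement.
- **That late limb measurement makes the compression inaccurate.** A given measuring error changes the finished garment equally whichever order is used. Reordering guards only against an arm-related error, and none is shown.
- **That one measurement set plainly serves all three garments.** Section 9.1.4.1.3 treats the DD-10 thumb differently when the pattern is made, so this has to be settled first.
- **That reordering cures loss after assignment.** The text has Therapist A go on to Time 1 with no stated gap. The evident loss window is the fabrication wait of up to 7 days and the 30-minute try-on, and both stay after assignment under either order.

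What survives is that recording Time 1 first protects those scores whether or not masking holds.

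**Conclusion.** The point holds as an avoidable risk. Section 9.1.5 unambiguously places assignment before the Time 1 outcome scores and the garment measurement. It routes the sequence number through the assessor of the primary outcome and leaves open whether that number reveals the arm. No other section reverses the order.

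Its size cannot be fixed from the document. At N = 132, with an assumed correlation of 0.5 and an assumed 0.2 SD shift in one arm at Time 1 only, the 5% error rate becomes about 14%. With masking intact it remains 5%. The sample size of 132, inflated to 165, is not in question. This is a free improvement to the conduct of the trial, not evidence that its primary comparison is invalid.

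**What to change.** Reorder section 9.1.5 as follows:

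1. Consent, screening and the Demographic Form are completed.
2. All six Time 1 instruments (FMA, BBT, MAS, VAS, DASH, SF-36) are completed and recorded.
3. Only then does Therapist A report to the researcher that the participant is ready for assignment.
4. The researcher assigns the arm and passes it to the fabricator only. State explicitly that Therapist A receives neither the arm nor its code. This part also protects the Week 4 and Week 8 scores, which the reordering alone would not.

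Take the garment measurement before assignment as well, provided a common measurement set is first reconciled with the DD-10 thumb handling in section 9.1.4.1.3. If it cannot be, say which measurement depends on the arm and who takes it.

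The cost is one rewritten paragraph and, for the measurement, one clarification. No visit or sample size is added, and fabrication already follows measurement. The change should be in place before the first participant is assigned, because a Time 1 score taken after assignment cannot be re-collected.

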#### 9.1.4.1.4 Single-Layered No Circumferential Reduction (S-0) Pressure Garment

S-0 is pressure-free pressure garment designed to be used as a control/placebo for this study. S-0 involves mainly the same fabrication process as SS-10 except it takes the value of 0 in the ratio of reduction. Thus, participants the control group will not feel constricted/compressed while wearing this pressure garment, as shown in the Figure 7.

[figure not shown]

Figure 7 Single-layered no circumferential reduction (S-0) pressure garment

Considering that pressure garment need to be washed regularly to ensure cleanliness and hygiene, and to prevent the growth of bacteria, each participant in this study will

be provided with two sets of identical pressure garment for easy replacement and cleaning.

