### **9.1.6 Data Analysis**

Data will be analysed using SPSS 26.0 using Intention-to-treat (ITT) analysis. ITT analysis, which aims to minimize bias and maintain random allocation of study participants (Gupta 2011), is suitable to be used when there are shedding participants. Its key idea is to analyse the group to which the participant belongs in that initial allocation, regardless of whether they completed the study or received the intended intervention. In clinical trials, participants may drop out, refuse intervention, or deviate from the study protocol. The ITT analysis includes all participants regardless of whether they completed the study or followed the treatment plan. This helps prevent shedding bias, which may occur if only completers are analysed (Mccoy 2017). The study will use a imputation method, such as, Last Observation Carried Forward (LOCF) (Shao & Zhong 2003) or mean imputation (Jadhav et al. 2019), or multiple imputation (Austin et al. 2021), this will probably depend on the requirements of the data.

Both descriptive and inferential statistics will be used. Frequencies, means, and medians will be used to describe the demographic data (Fisher & Marshall 2009). A mixed model ANOVA to compare the outcome measures.

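### Enrolment is placed both before and after randomisation, and the later, tolerance-based point is not reconciled with the intention-to-treat statement

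*Protocol*

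**What the plan says.** Protocol section 9.1.5 sets this order: screening and consent, enrolment, allocation, baseline, garment measurement, fabrication, try-on, formal enrolment.

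- Allocation follows a first enrolment: "After participant enrolment, Therapist A will report to the researcher to obtain the randomization sequence number generated using SPSS 26.0". Then: "The researcher will assign the participant into either S-10 (intervention group), DD-10 (intervention group), or S-0 (placebo group) according to the sequence list".
- Baseline (Time 1) and the garment measurements are taken next, by Therapist A, who is described as blinded.
- The custom garment is then delivered and tested: "within 7 days after pressure garment measurement), the participant will try it on for 30 minutes, under the supervision of Therapist B".
- Entry is decided only at that point: "The participant will formally be enrolled in the study if he/she does not experience allergy, oedema, pain or any other discomfort".

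Three other places bear on this. Section 9.1.4.1.4 says of the placebo garment that "participants the control group will not feel constricted/compressed while wearing this pressure garment". Exclusion criterion 4 in section 9.1.2.1 bars people with allergy to, or significant discomfort from, the garment materials. Section 9.1.6 bases the analysis on the initial allocation and adds: "The ITT analysis includes all participants regardless of whether they completed the study or followed the treatment plan".

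**The concern.** The garment tried on is made after the arm is assigned, so it is the assigned arm's garment. A pass-or-fail test on it is therefore an exclusion after randomisation that can depend on treatment. If those who fail are treated as never having entered, the groups compared are no longer the groups randomised. They are the subsets that tolerated their own garment.

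Two things are at stake. The first is the validity of the comparison of DD-10 and S-10 with S-0, including on the primary outcome (Fugl-Meyer, upper extremity). The second is information: how many people cannot tolerate each garment bears on the choice between designs, and that count would not appear in a report that starts from formally enrolled participants.

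**Working it through.** **1. The passages side by side.**

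- Section 9.1.5 uses enrolment for two events, one on each side of randomisation.
- Section 9.1.6 includes all participants by initial allocation. Whether a randomised person who fails the try-on counts as a participant depends on which enrolment is meant, and the protocol does not say.
- The thresholds also differ. Exclusion criterion 4 speaks of significant discomfort, while the try-on rule covers discomfort of any kind.
- Nothing in the text says whether try-on failures are followed, counted, analysed or replaced.

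**2. Dependence on arm.** The gate is the same for all arms, and S-0 can lose people too, for example through allergy to the fabric. However, DD-10 and S-10 are built with a 10% reduction, whereas S-0 wearers "will not feel constricted/compressed while wearing this pressure garment". Higher failure in the compression arms is a reasonable inference, not a stated rate.

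**3. The plan's sample size.** Inputs from section 9.1.2.3: f = 0.125, alpha = 0.05, power 0.8, three groups (k), three measurements (m), 20% dropout. Assumed here, because the text does not state them: correlation rho = 0.5 and sphericity (epsilon = 1).

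- Group-by-time interaction: lambda = f² × N × m / (1 − rho) = 0.015625 × 132 × 3 / 0.5 = 12.375.
- df1 = (k − 1)(m − 1) = 4; df2 = (N − k)(m − 1) = 129 × 2 = 258.
- Power = 0.808, and 132 is the smallest multiple of three that reaches 0.8.
- Inflation: 44 / (1 − 0.2) = 55 per arm, 165 in total.

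The stated figures reproduce.

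**4. Can the allowance cover try-on failures?** The list has 165 numbers, so the allowance is 165 − 132 = 33 losses after randomisation. Suppose 5% to 15% of the 110 compression participants fail and nobody in S-0 does (an assumption). That is 5.5 to 16.5 people, which is within 33. It leaves 27.5 to 16.5 losses for later dropout before the evaluable number falls below 132.

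**5. Bias.** Let e_c and e_0 be the failure rates in the compression and S-0 arms. Let d be the amount, in SD, by which excluded people would have changed less from baseline than retained people. Assume the same d in each arm and no true effect. Dropping failures moves an arm's mean by e × d, so the contrast moves by d × (e_c − e_0).

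| e_c | e_0 | d = 0.25 | d = 1.0 |
|---|---|---|---|
| 5% | 0% | 0.013 | 0.05 |
| 10% | 2% | 0.02 | 0.08 |
| 20% | 5% | 0.038 | 0.15 |

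Every input is assumed. If d is negative, the sign reverses. A difference already present at baseline cancels from the group-by-time contrast, so only a difference in change counts. The table shows the mechanism and does not estimate the bias in this trial.

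**The case against.** The best defence is that no sentence removes try-on failures from the analysis. Section 9.1.6 keeps people by initial allocation even if they did not receive the intended intervention, and a randomised person who fails the try-on fits that description. A statistical analysis plan, not shown here, may define the analysis set. This stands to the extent that the loss of intention-to-treat is a reading of the text rather than a stated rule. It does not dispose of the point. Someone never formally enrolled is naturally read as outside the study, and no analysis plan can recover Week 4 and Week 8 data that were not collected. At best such people would have baseline values and entirely imputed outcomes.

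A reader might also infer four stronger things, none of which the documents support:

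- **That S-0 is not filtered.** The try-on rule applies to every arm.
- **That power falls to 0.76–0.79.** This requires taking out the assumed failures and then applying a fresh 20% to those who remain (159.5 × 0.8 = 127.6; 148.5 × 0.8 = 118.8). Since 165 is the number randomised, the 20% is more naturally counted from randomisation.
- **That 55 per arm cannot be reached.** The list still randomises 55 per arm; the evaluable target is 44.
- **That the exclusions favour compression.** This requires excluded people to have worse outcomes, and nothing in the protocol establishes that.

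Taking baseline after allocation is a lesser matter. The assessor is described as blinded and no garment yet exists.

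**Conclusion.** The concern holds as a defect in the definition of enrolment and in the handling of people randomised but not formally enrolled. As written, section 9.1.5 permits exclusion after randomisation on a criterion that plausibly depends on arm, and this is not reconciled with section 9.1.6 or with exclusion criterion 4. The effect on the compression-versus-S-0 comparison is unknown in direction and size, because the protocol gives neither failure rates nor any information on how such people would fare. The sample size of 132 evaluable and 165 randomised is not shown to be wrong. The conclusion rests on the natural reading that a person not formally enrolled is not followed. If all randomised people are meant to be kept, the protocol needs to say so before recruitment, because missed follow-up cannot be collected later.

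**What to change.** Reconcile sections 9.1.2.1, 9.1.5 and 9.1.6 as follows:

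1. Define enrolment once, as the moment the sequence number is issued, and drop the second use of the term.
2. State that every randomised participant stays in the intention-to-treat set in the allocated arm, and that those who fail the try-on are invited to the Week 4 and Week 8 assessments.
3. Report the number of try-on failures, with reasons, by arm.
4. Complete all baseline measures before Therapist A requests the number.

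The clinical rule on who goes on wearing a garment is untouched.

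The cost is a change of wording, a few extra follow-up visits and a slightly diluted effect estimate. One detail needs care. Section 9.1.5 times the follow-up assessments from garment removal, so it must state the timing for people who wear none. It must do so in a way that does not reveal their status to Therapist A, who assesses them and is later asked to guess the group.

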#### **9.1.4.4 Pressure Garment Application Form (Appendix J)**

The Pressure Garment Application Form is a self-developed form that includes items pertaining to pressure garment application including wearing time of pressure garment, frequency and length of occupational therapy session, and caregiver participation, etc. This form will be filled out by the participants or their family member on a daily basis and will be supervised by their therapists.

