During Phase IA, i.e., the first four weeks between Time 1 (Baseline) and Time 2 (Week 4), when participants are hospitalized in the rehabilitation department of the hospital, he/she will be required to attend an occupational therapy session conducted by Therapist B once a day for 30 minutes, 5 days a week. During Phase IB, i.e., the second

four weeks between Time 2 (Week 4), and Time 3 (Week 8), when participants were being discharged from the hospital. Although they need to continually wearing the pressure garment according to same wearing schedule, they will not need to attend occupation therapy session.

Each participant will be given a Pressure Garment Application Form (Appendix K) to complete. The form will need to be returned to the researcher during Time 2 (Week 4) assessment. A new form will be given for the participant to complete and collected by the researcher during Time 3 (Week 8) assessment. Therapist B will constantly monitor the condition of the pressure garment to make sure it stays tightly fit throughout the study. Depends on the garment condition, torn or loosed pressure garment will be repaired or replaced using a new pair of garments.

For Time 2 (Week 4) and Time 3 (Week 8) assessments, the FMA, MAS, BBT, and VAS will be performed by Therapist A. The DASH and SF-36 will be administered by Therapist A and completed by the participant; however, if needed, it can be completed with the help of a caregiver or a therapist. The MAS will be assessed immediately after removal of the pressure garment, and the DASH, and SF-36 will be completed within 30 minutes of removal. The order of assessments will be determined by drawing a ballot. The FMA, BBT, VAS will be assessed 30 minutes after removal and the order of assessment will also be determined by drawing a ballot.

Phase IA = Pressure Garment + Occupational Therapy for 4 weeks

Phase IB = Pressure Garment for 4 weeks

Therapist B, a treating therapist will provide a list of specific occupational therapy interventions, identified in this study as representing routine practice to participants. Therapist B will record the Pressure Garment Application Form (Appendix K). These specific occupational therapy interventions will be given according to the following sequence:

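### After the 30-minute try-on, the protocol as shown has no structured, wear-specific record of pain, swelling or skin reaction, and its pain scale is read 30 minutes after the garment comes off

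*Protocol*

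**What the plan says.** **Exposure.** Protocol 9.1.5 sets wear "for 3 hours in the morning, 3 hours in the afternoon, and 8 hours at night each day for 8 weeks". Occupational therapy runs five days a week in the first four weeks, in hospital. In the second four weeks participants are discharged, keep the same wearing schedule and have no therapy sessions.

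**Tolerance check.** Once the garments are made, "the participant will try it on for 30 minutes, under the supervision of Therapist B", and "The participant will formally be enrolled in the study if he/she does not experience allergy, oedema, pain or any other discomfort". This step comes after the researcher has assigned the group and after the baseline assessment.

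**Recording during wear.** Section 9.1.4.4 describes a daily form covering "wearing time of pressure garment, frequency and length of occupational therapy session, and caregiver participation, etc". The columns in Appendix J are date, daytime and night use, treatment frequency, duration and location, therapist, carer participation and remarks. Section 9.1.5 adds that "Therapist B will constantly monitor the condition of the pressure garment to make sure it stays tightly fit throughout the study".

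**Pain outcome.** Hypothesis 4 (section 6.0) concerns pain on the VAS during the 8 weeks of application. At Weeks 4 and 8, "The FMA, BBT, VAS will be assessed 30 minutes after removal". DASH and SF-36 are completed within 30 minutes of removal, and the muscle-tone scale is scored immediately after removal.

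**Control garment.** Section 9.1.4.1.4 describes S-0 as pressure-free, so that control participants should not feel compressed.

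**The concern.** The protocol treats limb reactions as serious enough to decide whether a participant formally enters the study, and then stops asking about them in any structured way once long-term wear begins. The trial compares two compressive garments with one designed to exert no pressure, so comfort and reactions during wear are where the arms can be expected to differ. As written, the trial could report on motor function, dexterity, tone, garment-off pain and quality of life, but it would have no systematic comparison of how the garments were tolerated. That gap cannot be closed at the analysis stage, because no analysis plan can recover items that the forms did not collect.

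**Working it through.** **1. Planned exposure (section 9.1.5).** 3 + 3 + 8 = 14 hours a day. Over 8 weeks, 14 × 56 = 784 hours. Each four-week phase holds 14 × 28 = 392 hours, so 392 hours fall in Weeks 5 to 8, when no therapy session is scheduled.

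**2. What is recorded, and when.**

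| Item | At try-on | During wear | At Weeks 4 and 8 |
|---|---|---|---|
| Allergy or skin reaction | checked by name | no prompt; remarks column only | no instrument |
| Oedema | checked by name | no prompt; remarks column only | no instrument |
| Pain | checked by name | no prompt; remarks column only | VAS 30 minutes after removal; SF-36 pain and DASH symptoms within 30 minutes of removal |
| Garment condition and fit | – | monitored by Therapist B | – |

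The monitoring duty concerns the garment. No check of the limb is specified for any period after the try-on.

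**3. Which participants the compared groups contain.** The order in section 9.1.5 is assignment, baseline, measurement, fabrication, try-on, formal enrolment. A participant who reacts to the assigned garment at the try-on is therefore lost after assignment. Unless these participants are counted in the arm assigned, the earliest intolerance also drops out of the comparison.

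**4. What the garment-off VAS could miss (illustration).** The protocol gives no rate at which in-wear pain fades, so a range is shown.
- From section 9.1.2.3: 132 evaluable participants in three groups, 132/3 = 44 per arm. The plan's inflation for 20% dropout reproduces: 44/(1 − 0.2) = 55 per arm, 165 in total.
- Assumed: a true in-wear difference between two arms of d = 0.5 or 0.8 SD; a fraction r of it still present 30 minutes after removal; a two-sided 5% test of two means.
- Formula (normal approximation): power = Φ(d × r × √(44/2) − 1.96).

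| In-wear difference | r = 1 | r = 0.5 | r = 0.25 |
|---|---|---|---|
| 0.5 SD | 65% | 22% | 9% |
| 0.8 SD | 96% | 47% | 15% |

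For example, with d = 0.5 and r = 0.5: 0.25 × 4.690 − 1.96 = −0.787, and Φ(−0.787) = 22%.

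**5. Monitoring text.** Section 9.1.5 has Therapist B monitoring constantly and for the whole study. The same section ends the therapy sessions at Week 4 and describes no other contact before the Week 8 assessment.

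**The case against.** A reader might go further and infer that nothing captures garment-related pain, that problems at home go unrecorded, or that a painful garment would look equal or even better. The documents do not support these readings.

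- **Pain is measured.** It is rated on the VAS at Weeks 4 and 8, and SF-36 (section 9.1.4.3.6) and DASH (section 9.1.4.3.3) include pain and symptoms. Only the VAS is tied to 30 minutes after removal. The DASH and SF-36 forms are not reproduced, so their recall periods cannot be read here.
- **Problems can be written down.** A new daily form is issued for Weeks 5 to 8, it has a remarks column, and section 9.1.4.4 has therapists supervise its completion. What is missing is a prompt.
- **Contact exists in Weeks 1 to 4.** Five sessions a week for four weeks is 20 sessions in which a therapist could notice a reaction. In Weeks 5 to 8 no session is scheduled, but the text does not rule out other contact.
- **Garment-off assessment is a coherent choice.** FMA, BBT and VAS share the same timing, and hypothesis 4 does not say that pain is to be rated during wear.
- **Some material is not visible.** The VAS form shows two end labels, with no body site or time frame, but its wording may be incompletely extracted. The SPIRIT figure and the consent material cannot be judged.
- **No bias is shown in the trial's outcomes.** The try-on is 0.5/784 = 0.06% of planned wear, but that ratio counts neither missed events nor bias. Nothing in the protocol shows that unrecorded discomfort would improve a garment's FMA result.
- **Wearing experience is explored elsewhere.** Sections 2.0 and 5.0 make it an aim of the wider project, though through participants' perceptions and not as a between-arm measure.

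All of this limits the point to structured, wear-specific recording. None of it supplies prompted data on swelling, skin reaction or pain during wear.

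**Conclusion.** The point holds in this limited form. In the protocol as shown, 784 planned hours of wear per participant follow the try-on with no prompted record of pain during wear, swelling or skin reaction, and the designated pain outcome describes the arm with the garment off. SF-36 pain and DASH symptoms give partial cover that, as described, is not specific to wear. A tolerability difference between the compressive and pressure-free garments is foreseeable from the protocol's own description of S-0, and it could go undetected. How much the VAS would miss depends on how fast in-wear pain fades; the power range of 9% to 65% for a 0.5 SD difference is an illustration under assumed inputs, not an estimate. The sample size is not affected. The change is a cheap improvement and is best made before data collection starts, because the data cannot be recovered afterwards.

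**What to change.** 1. Add prompted daily items to the existing Pressure Garment Application Form: skin problem, swelling, pain while wearing, numbness or colour change, and early removal with the reason. Collect the form at Weeks 4 and 8, as already planned.
2. At Weeks 4 and 8, add one VAS rating of pain in the affected arm while wearing the garment, with body site and time frame stated on the form. Keep the garment-off VAS as it is.
3. Report these data by assigned arm, and count participants who fail the try-on in the arm to which they were assigned.
4. Reconcile the constant, study-long monitoring in section 9.1.5 with the absence of scheduled therapy sessions in Weeks 5 to 8. How any reaction is managed is for the investigators to set.

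The cost is a revised form, one extra rating at two existing assessments, and a small added burden on participants and data entry. No new visits or staff are needed.
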